# The College of Medicine, University of Malawi

# The Department of Pharmacology, Liverpool University, UK.

- The School of Tropical Medicine, Liverpool University, UK.
- Malaria Section, University of Maryland School of Medicine, USA

Executive Summary

The development of resistance to antimalarial drugs is of huge public health concern. In Malawi, sulphadoxine-pyrimethamine (SP) replaced chloroquine (CQ) in 1993 as the first line treatment for uncomplicated malaria because of high levels of CQ resistance (CQR). However SP-resistance is increasing. **Combination therapy (CT)** is proposed as a means of slowing the development of parasite resistance. Artesunate (ART) is suggested as an ideal drug for an anti-malarial combination. Recently, evidence has become available supporting the use of a non-ART CT as a possible alternative.

- There has been a marked decline in the incidence of *pfcrt* (a molecular marker for CQ resistance) in Malawi, suggesting a possible return to CQ sensitivity.
- Amodiaquine (AQ) in combination with SP has been shown to be efficacious and well tolerated in Uganda in an area of high-level CQ resistance.

This issue is of huge public health importance, as combinations of CQ or AQ plus SP would be considerably more affordable than any form of ‘artemisinin combination therapy’.

This study will use molecular tools to look for evidence that CT (both with and without artemisinin drugs) can slow the emergence of resistance genotypes in the study population based on our current understanding of antifolate and quinoline resistance mechanisms. Four different treatment regimes will be compared in a randomised clinical trial; ART-SP, CQ-SP, AQ-SP and SP alone. The prevalence of known resistance alleles will be compared between parasites present in the original infection and those appearing after treatment and attempts will be made to distinguish recrudescent infections from re-infections. To address the possibility that treatment failure could have a pharmacokinetic basis, I will incorporate a population pharmacokinetic study. I will determine whether re-introduction of CQ in a combination leads to the rapid re-selection of *pfcrt* mutations. Clinical outcomes will be compared and the results reported to the National Malaria Control Committee in Malawi. Recently, several new resistance mutations have been identified in vitro associated with high levels of pyrimethamine resistance. To seek novel mutations in vivo, full sequencing of the known resistance associated genes will be performed on parasites in all cases of treatment failure not predictable by the pharmacokinetic data or parasite genotype.

**Background/Introduction**

In 1993, because of high levels of chloroquine resistance, Malawi switched from using Chloroquine as first line therapy for uncomplicated malaria to sulfadoxine-pyrimethamine. However, SP-resistance is increasing and currently in Malawi about 20% of SP treatments fail ([name], personal communication).

Combination therapy (CT) of two or more drugs working by different mechanisms is proposed as a means to delay development of resistance to anti-malarial drugs. An ideal combination rapidly reduces parasite biomass leaving only a small residual parasite population exposed to high concentrations of the second drug[[1]](#endnote-2). Artesunate (ART), an artemisinin derivative, causes a rapid reduction in parasite biomass with a parasite reduction ratio in the range of 103-105 (ref. [[2]](#endnote-3)) and would be an ideal drug for an anti-malarial combination. In 1994, the introduction of an ART-mefloquine combination as routine treatment for malaria on the Thai-Burmese border (a low transmission area) improved clinical cure rates and brought about a return of in vitro parasite sensitivity to mefloquine[[3]](#endnote-4). In Africa, combination therapies, both with and without artemisinins, have been shown to be well tolerated and to have clinical benefit in terms of accelerated cure rate and symptom relief[[4]](#endnote-5) [[5]](#endnote-6)**.**

The development of SP resistance in areas of high transmission is facilitated by its slow elimination permitting a prolonged period during which blood levels of the drugs exert selection pressure for resistance[[6]](#endnote-7). Both sulfadoxine (Sd) and pyrimethamine (Pm) exert their anti-malarial effect by interrupting *P.falciparum* folate metabolism; they are always used in synergistic combination. Pm competes for the active site of the parasite enzyme dihydrofolate reductase (DHFR) and Sd competes for dihydropteroate synthase (DHPS). Four point mutations at codons 108, 51, 59 and 164 on DHFR are well established for their ability to decrease parasite sensitivity to Pm and are associated with in vivo resistance[[7]](#endnote-8). DHPS gene point mutations at codons 437, 436, 581, 540 and 613 are associated with a decreased susceptibility to Sd, although the relevance of sulfadoxine resistance to clinical response after SP is less clear[[8]](#endnote-9). SP use is associated with the disappearance of fully drug-sensitive parasites and a significant increase in the number of point mutations conferring resistance in both the DHFR and DHPS genes in subsequent parasitaemias (re-infections or recrudescents) occurring within 42 days of treatment[[9]](#endnote-10).

Novel DHFR mutations may also exist in vivo that confer increased resistance. A yeast-based system with the DHFR gene inserted has allowed the screening of over 1000 functional DHFR alleles to determine their sensitivity to Pm. New mutations on the DHFR domain have been identified that increase resistance to Pm by 10-100 fold in vitro[[10]](#endnote-11). This work raises the possibility that other novel resistance mutations are present contributing to in vivo resistance.

Mutations in the gene *pfcrt*, which encodes a transmembrane protein in the digestive vacuole of the malaria parasite, have recently been demonstrated as being strongly associated with CQ resistance (CQR). Several mutations have been identified but the K76T mutation appears critical. As a molecular marker for CQR in vivo, this mutation is almost 100% sensitive and 40–50% specific[[11]](#endnote-12) [[12]](#endnote-13), and it has been shown to confer resistance in genetic transformation studies[[13]](#endnote-14). Another gene, pfmdr1, encoding Pgh-1, a food vacuole glycoprotein, has been suggested as also having a role in modulating CQR[[14]](#endnote-15). Many polymorphisms of this gene have been described but the N86Y mutation has been the most investigated in Africa. Some studies have shown associations between this mutation and in vivo CQR but others have not[[15]](#endnote-16).

Amodiaquine (AQ), another 4-aminoquinolone, was widely used in the past to treat and prevent malaria but concerns about its safety led to its withdrawal as a first line agent. In the face of increasing levels of CQ and SP resistance, the use of AQ is increasingly being proposed in Africa. AQ has superior antimalarial activity to CQ and cross-resistance to CQ although present (especially to the active desethyl metabolite of AQ) is small[[16]](#endnote-17). A review of AQ treatment for uncomplicated malaria did not identify any additional side-effects or toxicity when compared to CQ or SP treatment[[17]](#endnote-18).

**Rationale/Justification**

In parts of East Africa, high levels of CQ resistance may limit its effectiveness in combination therapies. Although CQ resistance has been thought to be common and stable in Malawi, recent data open this to question. The chloroquine resistance conferring mutation K76T in the gene *pfcrt* had a prevalence of 85% in Malawi in 1992 shortly before SP replaced CQ as first line therapy. Recent work has shown that this prevalence has fallen to around ~13%, suggesting a return to CQ sensitivity ([name]; personal communication)*.* Recently, over 50 Malawian adults with asymptomatic parasitaemias were treated with CQ alone and all but one (whose parasitaemia could be due to re-infection) cleared their parasitaemia ([name]; personal communication). Another study using parasites from Malawian children in 1998 noted a significant reduction in the proportion of CQ resistant isolates on in vitro testing compared to a similar study in 1988, suggesting a possible recovery of CQ sensitivity after long-term absence of drug pressure[[18]](#endnote-19).

There is merit in examining the possibility that, in Malawi, CQ in combination with another drug such as SP might offer clinical benefit as well as a reduction in the rate of development of SP resistance. Reintroduction of CQ as a single agent is likely to re-select the *pfcrt* mutation but, in combination with SP, selection of CQ resistance may also be prevented or delayed. The involvement of *pfcrt* in parasite susceptibility to AQ has not been addressed and the role of non-K76T *pfcrt* mutations in determining CQR needs further evaluation. The relationship between *pfmdr1* and clinical outcome remains to be clarified.

ART has a very short half-life (60mins) and rapidly leaves the second drug in a combination unprotected. From a pharmacokinetic point of view, closer matching of the elimination half-lives of drugs in a combination may reduce the selective pressure for resistance in high transmission areas. Both CQ and AQ have pharmacokinetic profiles closer to SP than ART and also achieve rapid reductions in circulating parasitaemia with parasite reduction ratios in the range of 102-104 (ref.2). If the theoretical arguments in favour of CT therapy are accepted, AQ in combination with SP should be an effective and affordable alternative for Africa. In support of this a combination of AQ with SP has recently been shown in Uganda to be highly effective with no increase in adverse effects reported[[19]](#endnote-20).

In comparing malaria treatments it is important to distinguish whether parasites appearing after treatment are due to re-infection or recrudescence. In this study, polymorphic loci (microsatellite markers) on the *P. falciparum* genome will be compared pre and post treatment to determine as accurately as possible whether parasites are recrudescent or new. One protocol characterising twelve polymorphic loci has been previously described[[20]](#endnote-21). The use of microsatellite markers will enable the study to be controlled for the potential complications of non-clonal infections. To address whether treatment failure can be explained by inadequate treatment, drug plasma concentrations will be measured in all patients and population pharmacokinetic models established. Novel DHFR mutations conferring increased *in vivo* resistance will be looked for in patients with treatment failure despite adequate drug concentrations and whose parasite genotype suggests sensitivity.

# Objectives of the study

In the treatment of uncomplicated *P falciparum* malaria, the following hypotheses will be tested: -

1. Compared to the standard regimen of SP alone, the addition of CQ or AQ or ART to SP results in:

- Improved clinical outcome in this clinical setting.
- Decreased selection of resistance mutations in the dihydrofolate reductase (DHFR), dihydropteroate synthetase (DHPS), *pfcrt* and *pfmdr1* genes in new and recrudescent infections occurring up to 42 days after treatment.

1. Use of CQ in combination with SP does not lead to a rapid re-selection of *pfcrt* mutations.
2. Treatment failures not predictable by genotype or pharmacokinetic data are associated with novel DHFR, DHPS, *pfcrt* and *pfmdr1* mutations.

**Methods**

### Type of study

A randomised clinical trial comparing SP plus placebo to SP plus one of CQ, AQ and ART over a standard 3 day regime. All patients will be followed up using a modified version of the WHO in-vivo protocol, the clinical end-points being acceptable clinical response (ACR), early treatment failure (ETF) and late treatment failures (LTF)[[21]](#endnote-22). Children, who become unwell from days 15 to 42 post treatment, will remain under follow up in the study. Children who develop severe malaria while in the study will receive quinine treatment as is standard in Malawi. Children with treatment failure but no severe symptoms will be treated with *Co-Artem* (Artemether plus lumefantrine). The tolerability of the four regimes will be assessed by symptom enquiries from the patients. Laboratory and clinical staff will be blinded to the treatment groups.

Place of study

The children will be recruited and followed up from Chilomoni Health Centre, which is situated in a peri-urban area of Blantyre.

Study population

Children aged 12 to 60 months. Entry criteria will include a pure mono-infection (on microscopic grounds) of *P falciparum* with parasitaemias ranging from 20,000 to 200,000 L-1 and no clinical feature suggestive of severe malaria[[22]](#endnote-23).

Study period

A continuous 2-year period in Malawi starting in March 2003.

Sample size

500 children will be recruited. The sample size has been determined to detect the difference between an ACR rate of 80% with SP alone and 95% with CQ-SP using p=0.05 and a type 2 error of 10%. Each arm of the trial will have 125 children, which allows for a 25% loss to follow up rate. To obtain rich data for the pharmacokinetic study, a further 12 older children will be recruited for each trial arm, and treated unblinded.

Data collection

All patients will have a Case Record Form (CRF) completed: this will include details of a standardised history and examination, side-effect enquiries and the results of investigations. The CRF will be up-dated at every subsequent consultation.

A population pharmacokinetic (PK) model will be developed for each drug in the trial, Pm, Sd, CQ and AQ. Because the trial is blinded, it is necessary to collect four 5ml venous samples from each child to be sure of collecting adequate data on all four of the treatment regimes. The first sample will be taken within 3 hours of the initial drug dose, the second, third and fourth at random times on days 3, 7 and 14 when the children attend the clinic for review. To obtain rich PK data, a further 12 older children will be recruited for each trial arm, and treated unblinded. Seven 2ml venous samples will be collected following a defined schedule depending on which treatment regime they have received. Pm, Sd, CQ, desethyl-CQ, AQ and desethyl-AQ plasma concentrations will be measured on these samples by high performance liquid chromatography (HPLC) at the Wellcome Trust Research Laboratory in Blantyre. ART and dihydro-ART concentrations will be determined in Liverpool on stored samples by LC/Mass Spectrometry.

An initial blood film will be prepared from a finger-prick sample on recruitment. Subsequent blood films will be prepared from the venous samples collected as detailed above. Haemoglobin concentration, white cell count, platelet count, bilirubin, gamma-glutamyl transpeptidase and creatinine will be determined from the venous samples collected on days 0 and 14. Gametocyte count on day 7 will be documented on all patients.

PCR followed by allele-specific restriction digestion for known DHFR, DHPS, *pfmdr1* and *pfcrt* markers of CQ, Sd and Pm resistance will be completed on all pre treatment parasites and on all parasites appearing up to 42 days post treatment. The protocols for these analyses are described previously[[23]](#endnote-24)13 [[24]](#endnote-25). The genotype of treatment failures and parasites appearing between days 14 to 42 from each of the treatment groups will compared. Microsatellite markers on the *P. falciparum* genome will be analysed by PCR using protocols developed by [name]’s group (a collaborator on this proposal) to try to distinguish re-infection from recrudescence.

Full DHFR, DHPS, *pfcrt* and *pfmdr1* gene sequencing will be done on all parasites which appear up to 42 days post-treatment despite adequate plasma drug concentrations (judged using the population PK models), and in whom the genotype suggests sensitivity. By these methods I expect to be able to identify novel DHFR, DHPS and *pfcrt* mutations that may arise conferring resistance. The gene sequencing will be performed in collaboration with the University of Maryland sequencing facility.

Using the genotype and parasite clearance / reappearance data a PK / Pharmacodynamic model will be established to establish the interplay between parasite genotype / kill and PK.

###

Data management/analysis

A Data and Safety Management Board with a written constitution will be established at the start of the trial.

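### On the usual two-sided formula, 125 children per arm cover a loss to follow-up of about 19–20% at 90% power, not the stated 25%

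*Protocol*

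**What the plan says.** The Protocol's Sample size paragraph (under Methods) is the only place where the trial is sized. The total is fixed first: "500 children will be recruited". The contrast is "an ACR rate of 80% with SP alone and 95% with CQ-SP", and the error rates are given as "using p=0.05 and a type 2 error of 10" per cent. The number per arm and the allowance for loss follow in one sentence: "Each arm of the trial will have 125 children, which allows for a 25% loss to follow up rate".

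The paragraph does not give the number needed before loss, the formula or test behind it, whether the 5% is one- or two-sided, or how the allowance for loss was applied.

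**The concern.** The contrast, the error rates, the number per arm and the tolerated loss are presented as holding together, so they can be checked against each other. A base of 100 per arm, which is what the common formula returns, gives exactly 125 when multiplied by 1.25. But adding 25% to a number is not the same as allowing for the loss of 25% of the enlarged number: a quarter lost from 125 leaves fewer than 100.

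What is at stake is the power claimed for the only comparison the trial sizes, and that comparison bears on the first hypothesis in the Objectives, improved clinical outcome. If the allowance is overstated, a reader would believe that a 25% loss leaves 90% power when, on the usual formula, it leaves somewhat less.

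**Working it through.** **Inputs, all from the Sample size paragraph.** p₁ = 0.80, p₂ = 0.95, difference d = 0.15; α = 0.05; power 0.90; loss 25%; 125 recruited per arm, 4 × 125 = 500. Two-sided testing is my assumption (z = 1.960 and 1.2816). The mean proportion is 0.875, and p₁(1−p₁) + p₂(1−p₂) = 0.16 + 0.0475 = 0.2075.

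**1. Evaluable number needed, pooled normal formula.**

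n = [1.960·√(2·0.875·0.125) + 1.2816·√0.2075]² / 0.15² = (0.9167 + 0.5838)² / 0.0225 = 100.06

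That is 100 to the nearest whole child, or 101 rounded up. Power on this formula is 89.98% at 100 and 90.3% at 101.

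**2. Reproducing the stated 125.** 100 × 1.25 = 125 exactly (101 × 1.25 = 126.25, rounded up to 127). Dividing out the loss gives 100.06 / 0.75 = 133.4, so 134 (135 from a base of 101). On this formula the stated figure is recovered by multiplication and not by division.

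**3. Loss that 125 covers.** 1 − 100/125 = 20.0%; 1 − 101/125 = 19.2%.

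**4. Left after a 25% loss.** 125 × 0.75 = 93.75, about 94.

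**5. Power at 94 per arm, pooled normal.** (0.15·√94 − 0.9167) / 0.4555 = (1.4543 − 0.9167) / 0.4555 = 1.180, and Φ(1.180) = 88.1%.

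**6. Dependence on method.** Two-sided 5% unless noted. The exact powers enumerate all pairs of binomial outcomes.

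| Method | Needed per arm | ÷ 0.75 | Power at 94 |
|---|---|---|---|
| Pooled normal | 100.06 | 134–135 | 88.1% |
| Unpooled normal | 96.9 | 130 | 89.1% |
| Continuity-corrected | 113.0 | 151–152 | 83.0% |
| Arcsine | 92.6 | 124 | 90.4% |
| Fisher's exact test, exact power | – | – | 85.6% |
| Uncorrected chi-square test, exact power | – | – | 90.4% |
| Pooled normal, one-sided 5% | 82 | 110 | 93.4% |
| Continuity-corrected, one-sided 5% | 95 | 127 | – |

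The arcsine row is 3.2415² / (2·0.2381²) = 92.6, where 0.2381 = arcsin√0.95 − arcsin√0.80. At 100 evaluable per arm the exact power is 88.3% for Fisher's test and 92.1% for the uncorrected chi-square test.

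**The case against.** The strongest defence is that the paragraph names no method, and that some legitimate methods make its figures agree. Two-sided arcsine needs 93 per arm, and 93 / 0.75 = 124. A one-sided continuity-corrected calculation gives 95 / 0.75, or 127. If the 5% is one-sided, the pooled formula needs only 110 recruited. The exact result is more telling. The pooled normal figure of 88.1% approximates the power of the uncorrected chi-square test, and by enumeration that test has 90.4% power at 94 per arm and 90.1% at 93. This is not bought with a materially inflated type 1 error: at 94 per arm it is 5.00%, 5.03% and 4.27% for common response rates of 80%, 87.5% and 95%. It can also be said that a gap of about 2 points is small beside the uncertainty in the planning rates; the Background rests the SP failure rate of about 20% on a personal communication.

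Most of this stands, and it limits the point in three ways.

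- A reader might infer that the loss was certainly added as n × 1.25. The fit is exact and the explanation simple, but neither the base of 100 nor the inflation step appears in the Protocol, so it remains an inference. Steps 3 to 5 do not depend on it.
- A reader might infer that the trial cannot reach 90% power after a 25% loss. That is true on the pooled, unpooled and continuity-corrected formulas and for Fisher's test, but not for the uncorrected chi-square test or on the arcsine calculation.
- A reader might infer that a working limit of 20% on loss is needed. The Protocol ties no action to 25%, and the size of the gap does not call for one.

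The defence does not remove the point. The Protocol names neither arcsine nor a one-sided test, neither variant returns exactly 125, and the sentence as it stands gives the reader no means of telling which calculation makes it true. Nor is this a detail left for an analysis plan: the Protocol itself states the figures.

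**Conclusion.** The point holds as a minor correction. On the usual two-sided 5% pooled normal formula, the stated 25% loss and 10% type 2 error do not fit together at 125 per arm. The number covers a loss of 19–20%; after a 25% loss the type 2 error is about 12%. Recruitment for a true 25% loss would be 134–135 per arm, 9–10 more than planned. The shortfall in power is about 2 points on that formula (90 − 88.1 = 1.9), about 4 with Fisher's exact test (90 − 85.6 = 4.4) and 7 on a continuity-corrected calculation (90 − 83.0). It vanishes for the uncorrected chi-square test evaluated exactly.

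This rests on two assumptions that the Protocol neither states nor excludes: two-sided testing and the pooled normal formula. The trial remains adequately sized for its stated contrast on most readings; what needs correcting is the description of the margin.

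**What to change.** Keep 500 children and reword the sentence in Sample size, for example: 

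> 125 per arm allows for about a 20% loss (about 100 evaluable) at 90% power (two-sided 5%, pooled normal formula); with 25% loss, about 94 evaluable per arm give about 88% power (about 86% with Fisher's exact test).

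Name the base number, the test and the sidedness actually used. If the original calculation was arcsine, or was based on the exact power of the uncorrected chi-square test, say so instead; the 25% can then stay. The method must be named in either case, because 100 evaluable per arm give 90% on the pooled formula but 88.3% with Fisher's test.

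The cost is one sentence and a slightly less favourable stated margin. No more patients and no limit on loss are needed.

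### The last-listed hypothesis claims an association between unexplained treatment failure and novel mutations, but only the unexplained cases are fully sequenced, so the association cannot be estimated or tested

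*Protocol*

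**What the plan says.** **Status of the claim.** The Objectives section opens its list by saying that "the following hypotheses will be tested". The last item is "Treatment failures not predictable by genotype or pharmacokinetic data are associated with novel DHFR, DHPS", continuing to *pfcrt* and *pfmdr1*.

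**Who is fully sequenced.** Three sections address this:

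- Methods (Data collection): "gene sequencing will be done on all parasites which appear up to 42 days post-treatment despite adequate plasma drug concentrations", with adequacy judged from the population pharmacokinetic models, "and in whom the genotype suggests sensitivity". Both conditions must hold.
- Executive Summary: sequencing is for "parasites in all cases of treatment failure not predictable by the pharmacokinetic data or parasite genotype".
- Rationale/Justification: novel mutations, here of DHFR only, "will be looked for in patients with treatment failure despite adequate drug concentrations and whose parasite genotype suggests sensitivity".

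**What the other parasites get.** Methods (Data collection) plans "PCR followed by allele-specific restriction digestion for known DHFR, DHPS", *pfmdr1* and *pfcrt* markers on all pre-treatment parasites and on all that reappear by day 42. Microsatellite typing is also planned, to separate re-infection from recrudescence. No section plans full sequencing of any comparator isolate.

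**What is expected.** Methods anticipates that sequencing will identify novel mutations that may arise and confer resistance.

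**The concern.** An association needs the frequency of a variant in cases and in non-cases. Here the second frequency is not collected. The Protocol itself fixes which parasites are sequenced, so this is not a detail that a statistical analysis plan could settle later.

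At stake is what may be concluded from a variant found in the sequenced cases. It may be a cause of failure or ordinary background variation in the local parasite population, and the planned data cannot say which. Nor can they show whether it was already in the child's original infection, because the paired day-0 isolate is not fully sequenced.

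The case group also differs between sections. The Objectives, Executive Summary and Rationale speak of treatment failures. Methods admits any qualifying parasite appearing by day 42, which can include new infections.

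**Working it through.** **1. The comparison the hypothesis needs.** For any novel variant:

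| | Variant present | Variant absent |
|---|---|---|
| Unexplained cases (fully sequenced) | observed | observed |
| All other parasites (known-marker assay only) | not observed | not observed |

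The lower row is empty by design. Allele-specific digestion reports on the codons it targets, and microsatellites do not read these genes. No odds ratio, difference in frequency or test can be computed. This step needs no numerical assumption.

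**2. How easily a neutral variant turns up.** The Protocol states no figure for this hypothesis, so there is none to reproduce. Let f be the background frequency of a neutral variant and m the number of cases sequenced, treated as independent. Both are assumptions.

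P(seen at least once) = 1 − (1 − f)^m

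For example, f = 0.05 and m = 5 give 1 − 0.95^5 = 0.23, and f = 0.20 and m = 10 give 1 − 0.80^10 = 0.89.

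| f | m = 5 | m = 10 | m = 20 |
|---|---|---|---|
| 5% | 0.23 | 0.40 | 0.64 |
| 10% | 0.41 | 0.65 | 0.88 |
| 20% | 0.67 | 0.89 | 0.99 |

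**3. Context for m.** The Sample size section gives ACR rates of 80% (SP) and 95% (CQ-SP), 125 children per arm and 25% loss. Taking 95% for AQ-SP and ART-SP as well is an assumption.

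- All 500 children: 0.20 × 125 + 3 × 0.05 × 125 = 43.75, about 44 failures.
- After 25% loss, 93.75 per arm: 0.20 × 93.75 + 3 × 0.05 × 93.75 = 32.8, about 33 failures.

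Unexplained failures are a subset of these. The total does not bound the Methods set, which also admits reappearing parasites that are not failures.

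**4. What comparators would allow.** The table gives the exact probability that a one-sided Fisher test reaches p ≤ 0.025, with two comparators per case. All frequencies are assumed.

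| Cases / comparators | Neutral variant declared associated (f = 5%, 10%, 20%) | Power, 50% of cases v 10% of comparators |
|---|---|---|
| 5 / 10 | 0.001, 0.003, 0.008 | 0.26 |
| 10 / 20 | 0.0004, 0.002, 0.006 | 0.47 |
| 20 / 40 | 0.003, 0.007, 0.013 | 0.88 |

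These probabilities are for one variant. Comparators make a test possible and rarely flag a given neutral variant, but power is low with 5 to 10 cases even for a large contrast.

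**The case against.** **This is discovery work.** Sequencing only the unexplained cases is a legitimate way to find candidates, and the Executive Summary and Rationale describe it as a search. That stands. The defect lies in the Objectives, which promise a test of association, and in the Methods expectation about resistance, which is itself hedged by saying such mutations may arise.

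**A neutral variant need not mislead.** A reader might infer that any harmless polymorphism will look like a resistance mutation. The documents do not support that. The variant must first occur among the few parasites sequenced, synonymous or catalogued changes can be set aside, and no rule equates one sighting with resistance. For DHFR, the Background cites in vitro evidence against which a variant could be read, though not for the other three genes. What remains is that a neutral variant cannot be told apart using the planned data.

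**New infections may be relevant.** A reader might infer that cases should be limited to recrudescences. The first hypothesis expressly covers new as well as recrudescent infections, and a new infection that establishes despite adequate drug is itself informative. The objection to excluding them stands. The mismatch in case definition is real but minor.

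**Comparators may not rescue the test.** This largely stands: power is 0.26 to 0.47 with 5 to 10 cases in the example, and testing many variants across four genes would need multiplicity control.

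**Conclusion.** The point holds. The association cannot be estimated or tested, because no parasite outside the case group is fully sequenced. That follows from the Protocol's text alone.

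The size is illustrative only: with an assumed 5 to 10 cases and an assumed background frequency of 5% to 20%, a neutral variant appears at least once with probability 23% to 89%. These are probabilities of a sighting, not of a false declaration.

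A reader might take about 44 failures as the number of cases. The documents do not support this: that figure ignores the planned 25% loss, assumes 95% ACR in two arms where it is not stated, and counts all failures, not the set that Methods would sequence.

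The matter should be corrected, but it is confined to a laboratory hypothesis. Randomisation, the ACR comparison and the known-marker selection analysis are untouched.

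**What to change.** **Either reduce the claim.** Reword the last hypothesis in the Objectives and the expectation in Methods as descriptive: identify and list candidate variants, with no claim of association or of conferring resistance. This costs wording only.

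**Or keep it and sequence comparators.** Fully sequence the four genes in:

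- day-0 isolates from children with ACR, a sensitive known-marker genotype and adequate drug levels, as the comparison group;
- each case's own day-0 isolate, to show whether the variant was already present, not as an independent control.

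Compare cases with the ACR comparators by an exact test, and state in advance that power will be low with few cases. The cost is modest extra sequencing. Day-0 isolates are already to undergo PCR for known markers in the same genes, and a sequencing facility is named, but availability of sufficient day-0 DNA is an assumption.

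**In both cases,** use one case definition in the Executive Summary, Rationale, Objectives and Methods. Report recrudescent and new infections separately, using the microsatellite typing already planned, instead of excluding new infections.
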